Clinical Research Protocol ver. 1.0

Created on April 20, 2018

Medical Science Research Implementation Plan

〔Subject for study〕

Effects of listening to music during dental treatment under intravenous sedation on autonomic nervous system, electroencephalogram, and psychological state.

1. Background of the study and basis for scientific rationality

Intravenous sedation and listening to music during dental treatment are widely accepted as methods for providing safe dental treatment. However, it is unclear how listening to music during dental treatment under intravenous sedation affects the human body and psychology.

The purpose of this study is to determine how listening to music during dental treatment under intravenous sedation affects electroencephalogram, autonomic nervous function, and psychological state. Previous research reports have revealed that it is linked to parameters of the autonomic nervous system, electroencephalogram, and circulatory dynamics as an indicator of relaxation, and it is a common evaluation item. Therefore, it can be said that this study has scientific rationality.

2. Purpose and Significance of the Study

The purpose of this study is to determine the effects of listening to music under intravenous sedation on electroencephalograms, autonomic nervous function, and psychological aspects. The subjects were 40 patients who visited Our University Hospital, who were judged by dentists to require intravenous sedation tooth extraction at the Our University Hospital, and who expressed their intention to participate in this study. The primary evaluation items were electroencephalograms, autonomic nervous function, and psychological aspects. If the results obtained can be feedback to the dental clinical field, it is believed that even patients who are anxious about dental treatment will be able to receive comfortable dental treatment. Systemic complications caused by mental stress, such as vasovagal reflex and hyperventilation attacks, which are likely to occur during dental treatment, can be prevented. Furthermore, it is believed that systemic complications such as increased blood pressure, tachycardia attacks, arrhythmia, and angina attacks during dental treatment can be prevented in patients with cardiovascular diseases such as hypertension and ischemic heart disease. Therefore, the significance of this study is also considered to be great in terms of safe dental care.

3. Selection policy for research subjects (collaborators)

Patients undergoing tooth extraction under intravenous sedation at the Our University Hospital General Management Dental Treatment Department

3.1. Eligibility criteria

① Diagnosis (including diagnostic criteria): Cases in which the dentist judges that tooth extraction under intravenous sedation is necessary

② Disease stage: Cases in which the dentist judges that acute symptoms have subsided

③ Age, gender: 20-40 yers, women

④ Outpatients

⑤ Target period (time of diagnosis, hospitalization, and outpatient visit): Time of diagnosis and time of treatment

3.2. Exclusion criteria

(Exclusion criteria for influencing efficacy evaluation)

① Cases with diseases that affect the autonomic nervous system or electroencephalogram

② Cases with a history of smoking

③ Cases taking medication regularly

4. Research Methodology

4.1 Details of Research Methods

1) Specify the Sample/Information to Be Used for the Research

1. Specific Details

Forty patients will be randomly assigned to two groups of 20 patients each: control and music　 using the envelope method. Patients in the music group listened to music during tooth extraction.

Patients whose dentist determines that a tooth needs to be extracted will be included in the study.

The Modified Dental Anxiety Scale (MDAS) will be administered before the start of the treatment.

The State Trait Anxiety Inventory-Trait Anxiety Scale (STAI) psychological test will be administered before and at the end of the procedure. Recording of heart rate variability and circulatory dynamic will begin 15 minutes before the start of the procedure while wearing headphones, and will be completed at the end of the procedure.

After optimal sedation concentration under intravenous sedation, the procedure is performed by the same surgeon, local anesthesia is administered, and tooth extraction is initiated.

Measurement analysis during tooth extraction with music listening through headphones will also be performed, and the two groups, the control group and the music group, will be statistically compared and analyzed using the analysis software GraphPad Prism6.

2. Period of Time to Be Collected (Be Specific)

Date of approval - March 31, 2023

2) Analysis Method

Statistical comparative analysis using analysis software GraphPad Prism6.

3)

1. Test Drug/Propofol

Test machine/ EEG and ECG real-time analysis system MemCalc/Makin2

Test method/ music during dental treatment under intravenous sedation.

2. Dosage/Treatment Intensity, etc. //The volume of the music should be at a level that does not cause distress to the patient. //If there is a marked change in vital signs as a criterion for changing the treatment intensity, etc., discontinue the treatment.

For intravenous sedation, follow the guidelines for intravenous sedation of The Japanese Dental Society of Anesthesiology.

The patient should be given intravenous sedation in accordance with the guidelines of The Japanese Dental Society of Anesthesiology.

3.Criteria for Deferral, Dose Reduction, Withdrawal, and Suspension

Discontinue if the subject complains or if there is a marked change in vital signs.

The patient should be given intravenous sedation in accordance with the guidelines of The Japanese Dental Society of Anesthesiology.

4. Discontinuation and Completion Criteria

Criteria for Adverse Events to Be Stopped, Deterioration of the Underlying Disease, etc., and Criteria for Completion of the Study /

Discontinue if subject complains or if a prominent change in vital signs is observed.

5. Acceptable Concomitant Therapy

None.

6. Unacceptable Concomitant Therapy

None

7. Treatment Restrictions after Completion of the Intervention

None

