4.2. Test schedule

All measurements will be taken on the day of treatment. A questionnaire will be conducted before and after the start of treatment. Parameters for autonomic nerves, electroencephalograms, and hemodynamics will be collected during treatment. Since no data will be collected before the test date, the number of days allowed for the test date to differ will not be determined.

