4.4. Target number of subjects and the basis for setting it

Number of cases: 40 cases who have given consent to this study

Bases for setting: α value 0.05, β value 0.2, effect size 1SD were used as the basis for setting the number of cases. It was set using Gpower.

5. Expected effects, side effects, or disadvantages to the study subjects, and responses to them and comprehensive evaluation of these

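### The only psychological questionnaire repeated after treatment is named as the STAI Trait scale, which is not designed to register a same-day change, although the study targets psychological state

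*Protocol*

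**What the plan says.** The title of the protocol gives the subject as "Effects of listening to music during dental treatment under intravenous sedation on autonomic nervous system, electroencephalogram, and psychological state". Section 2 adds: "The primary evaluation items were electroencephalograms, autonomic nervous function, and psychological aspects". It does not say which instrument represents the psychological item.

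Section 4.1 names two questionnaires:

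- For the first: "The Modified Dental Anxiety Scale (MDAS) will be administered before the start of the treatment". No later administration is given.
- For the second: "The State Trait Anxiety Inventory-Trait Anxiety Scale (STAI) psychological test will be administered before and at the end of the procedure".

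Section 4.2 fixes the timing with "All measurements will be taken on the day of treatment" and "A questionnaire will be conducted before and after the start of treatment". It does not name the questionnaire. The State form of the STAI is not named as an administered form anywhere in the protocol.

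Section 4.4 sets 40 patients, and section 4.1 splits them 20 and 20. The stated basis is "α value 0.05, β value 0.2, effect size 1SD were used as the basis for setting the number of cases". The test, its sidedness and the outcome to which the 1 SD applies are not given.

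**The concern.** The inventory's own name distinguishes two constructs. State anxiety is how the person feels now; trait anxiety is how the person generally feels. The title asks about the first, and section 4.1 selects the second. A disposition score taken twice within a few hours is a reasonable baseline descriptor, but a weak choice for detecting what music did during one extraction.

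This cannot be left to an analysis plan. The form handed to the patient determines what data exist, and no later analysis can recover a State score that was never collected. If staff follow the text, one of the three primary items rests on a measure of the wrong construct. A null result on it would say little about whether music helped.

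**Working it through.** **1. Which instrument can carry the psychological item?**

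| Instrument (section 4.1) | Before treatment | After treatment | Usable as a post-treatment outcome? |
|---|---|---|---|
| MDAS | yes | not planned | no |
| STAI, Trait Anxiety Scale | yes | yes | yes, but it scores trait |
| STAI, State form | not named | not named | not available as written |

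By elimination, the Trait scale is the psychological primary measure. This is an inference, because section 2 names no instrument, but it is the only candidate that the protocol leaves.

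**2. Does the timing help?** No. Section 4.2 places every measurement on the treatment day. The one-year follow-up listed in section 4.3 has no assessment attached to it.

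**3. The plan's own figure.** Section 4.4 gives alpha 0.05, beta 0.2 (power 80%), an effect of 1 SD and 40 patients. For a two-sided two-sample t-test:

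- 16 per arm gives power 78.1% and 17 per arm gives 80.7%, so the requirement is 17 × 2 = 34.
- A two-sided Wilcoxon-Mann-Whitney test with the minimum relative efficiency of 0.864 gives 79.2% at 19 per arm and 81.4% at 20 per arm, so 20 × 2 = 40. This matches the protocol.
- The t-test figure with an assumed 15% dropout also matches: 34 / (1 − 0.15) = 40.

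The protocol states neither that test nor a dropout rate. The figure of 40 is therefore attainable from the stated inputs, and the present point does not depend on it.

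**4. Illustration of what is at stake.** The protocol gives no expected effect on a trait score, so the standardized difference d is my assumption, shown as a range. The two-sided t-test is also assumed. With n = 20 per arm:

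- degrees of freedom = 2n − 2 = 38
- noncentrality = d × √(n/2) = d × √10 = 3.162d
- power = probability that a noncentral t variable with these parameters exceeds the two-sided 5% critical value in absolute size

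| True d on the scale used | Noncentrality | Power |
|---|---|---|
| 0 | 0 | 5.0% |
| 0.1 | 0.316 | 6.1% |
| 0.2 | 0.632 | 9.5% |
| 0.3 | 0.949 | 15.2% |
| 0.5 | 1.581 | 33.8% |
| 1.0 | 3.162 | 86.9% |

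At d = 0 the 5.0% is simply the false-positive rate. The 86.9% at d = 1.0 is what 20 per arm gives under this assumed test; the power that the protocol plans for is 80%.

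**The case against.** **The name may be a slip.** The abbreviation in section 4.1 is that of the whole inventory, and the wording of the protocol is loose elsewhere (mixed tenses in section 4.1, two sections numbered 17). With a title about psychological state and administration before and after, the writers may have meant the full STAI or its State form. This stands as a real possibility, and if it is so there is no loss of power, only a wrong name. It does not rescue the text, because staff who follow it would hand out the Trait form.

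**A reader might infer that a trait score cannot move at all.** The protocol reports no retest stability or responsiveness for either scale, and trait answers may shift a little with mood. What the scale's name supports is that it is not designed to register a same-day change.

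**A reader might infer that the trial is bound to conclude that music has no psychological effect.** The protocol fixes no decision rule for this item, and a non-significant result is not a finding of no effect.

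**The link to the sample size is loose.** Section 4.4 does not tie the 1 SD to the psychological item, so the drop in power is an illustration and not a recalculation of the plan.

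**The psychological measure might be defined elsewhere.** An analysis plan that is not shown may define the endpoint, and the unnamed questionnaire in section 4.2 leaves room for doubt. Neither would change the form that section 4.1 tells staff to administer.

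**Conclusion.** The point holds as a contradiction between the instrument named in section 4.1 and the construct named in the title. As written, one of the three primary items rests on a scale not designed to show a within-day change, and no other named instrument is given after treatment. The EEG and autonomic items are untouched.

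The size depends on an effect that the protocol does not supply. If music shifts the trait score by 0 to 0.2 SD, power for this item is about 5–10%, against 80% planned for 1 SD. At 0.3 SD it would be 15.2%. These figures rest on the assumed d, the assumed two-sided t-test at alpha 0.05, and 20 analysed patients per arm.

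The documents cannot settle whether the Trait form is truly intended or the name is a slip. Under the first reading it is a design fault that must be mended before data are collected; under the second it is a wording error. The sentence has to be changed in both cases.

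**What to change.** In section 4.1, name the STAI State Anxiety form as the psychological outcome, given to both arms before treatment and again when the procedure ends. If the Trait form is wanted, give it once before treatment, beside the MDAS, as a baseline descriptor or covariate. Say in section 2 that the State score represents the psychological primary item, and name the form in section 4.2, so that the sections agree.

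If any patients have already been enrolled, check which form they completed, because a State score that was not collected on the day cannot be reconstructed.

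The core change is a one-line amendment and a different questionnaire form, with no extra visits, patients or staff. The sample size stays at 40 if the 1 SD assumption is kept.

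### Any type of extraction is eligible, yet extraction type, duration and local anaesthetic use are not listed as recorded; this costs precision and leaves differences in surgery between the arms unexaminable.

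*Protocol*

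**What the plan says.** **Eligibility.** Protocol 3.1 admits "Cases in which the dentist judges that tooth extraction under intravenous sedation is necessary", provided acute symptoms have settled. Neither 3.1 nor 3.2 limits tooth, impaction, simple versus surgical technique, or expected duration. Section 4.1 repeats the criterion without narrowing it.

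**Allocation.** Section 4.1: "Forty patients will be randomly assigned to two groups of 20 patients each", by envelopes. No stratification factor is given.

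**Sequence and recording.** Heart rate variability and circulation are recorded from 15 minutes before the procedure until it ends. Within that period, once sedation is adequate, "the procedure is performed by the same surgeon, local anesthesia is administered, and tooth extraction is initiated". The analysis that 4.1 names is of measurements during the extraction, compared between control and music.

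**Data.** Sections 4.1 and 4.2 list the dental anxiety scale, the state-trait anxiety inventory and physiological signals: "Parameters for autonomic nerves, electroencephalograms, and hemodynamics will be collected during treatment". No operative or local anaesthetic variable is among them. Sedation is referred to a professional society guideline; local anaesthesia is referred to nothing.

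**Size.** Section 4.4: "Number of cases: 40 cases who have given consent to this study", based on "α value 0.05, β value 0.2, effect size 1SD".

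**The concern.** Section 2 makes autonomic function, EEG and psychological state the primary items. How much surgery a patient undergoes is a plausible driver of all three. The protocol seems to accept the general idea: it excludes autonomic disease, smoking and regular medication because they influence the efficacy evaluation, and it fixes the surgeon. It does not extend this to the extraction itself or to the injection that every patient receives during the recording.

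Two things are at stake. First, variation between extractions adds to outcome variance that could be removed cheaply. Second, no operator blinding is described. If operating time or supplementary injections differed by arm, the trial would have no listed data with which to see it. A later SAP can define analysis windows, but it may be unable to recover event times and case details that nobody wrote down, and it cannot stratify an allocation already made.

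**Working it through.** **1. The plan's own sample size**

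Inputs from 4.4: α = 0.05 (two-sided assumed, since sidedness is not stated), power 0.80, effect size d = 1.

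- Two-sided t-test: 16.71, so 17 per arm, 34 in total.
- Two-sided Mann-Whitney with minimum asymptotic relative efficiency 0.864: 16.71 / 0.864 = 19.35 (from the unrounded value), so 20 per arm, 40 in total.

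The stated 40 is therefore reproducible under a standard option, although 4.4 names neither a test nor a dropout rate. Two-sided t-test power at 20 per arm and d = 1 is 0.869. Nothing here shows the stated figure to be wrong.

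**2. Variance due to extraction type**

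The documents give neither the share of harder extractions (p) nor their effect (D, in within-type SDs). Both are assumed: p = 0.5, D from 0.5 to 1.

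Total variance = 1 + p(1 − p)D², in units of within-type variance. Share due to type = 1 − 1/(1 + p(1 − p)D²).

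- D = 0.5: total 1 + 0.25 × 0.25 = 1.0625; share 5.9%.
- D = 1: total 1 + 0.25 × 1 = 1.25; share 20%.

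**3. Power at 20 per arm (two-sided t-test)**

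If the 1 SD of 4.4 is a within-type SD, the effective size is d = 1/√(total variance).

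| Case | d | Power | n per arm for 80% |
|---|---|---|---|
| No added variance | 1.000 | 0.869 | 17 |
| D = 0.5 (+6.25%) | 0.970 | 0.848 | 18 |
| D = 1 (+25%) | 0.894 | 0.787 | 21 |

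If the planning SD already reflects the usual mix of extractions, power stays at 0.869. About 20% added variance can be absorbed before power nears 0.80 (0.803 at +20%).

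**4. Chance imbalance, as a cross-check**

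Hypergeometric, 40 patients, 20 per arm:

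- 20 harder cases: P(arms differ by ≥ 4) = 0.343; by ≥ 6, 0.113.
- 12 harder cases: 0.301 and 0.082.

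With D = 1, a gap of 4 in 20 moves the arm difference by 4/20 × 1 = 0.2 within-type SD, or 0.2/√1.25 = 0.18 total SD. The standard error of the arm difference is √(2 × 1.25/20) = 0.354, so this shift is 0.2/0.354 = 0.57 standard errors. A gap of 6 gives 0.3/0.354 = 0.85 standard errors. This is the variance of step 2 seen from another side, not a further harm.

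**The case against.** The strongest reply is that randomisation already deals with this. Chance imbalance in an unmeasured factor is part of the standard error and covered by α, as it is for any covariate. The population is already narrow (women aged 20 to 40, outpatients, no smoking history, no regular medication, one department, one surgeon), and the planning SD may well include ordinary variation between extractions. All of that stands, so the point concerns precision and documentation, not validity.

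Three stronger readings are tempting, and the protocol does not support them.

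- A reader might infer that the arms are compared over one stretch that pools injection, surgery and music. The span from 15 minutes before to the end is the recording period. The analysis named in 4.1 is during extraction, and local anaesthesia comes before that. How the recording is cut into windows may properly be left to an SAP.
- A reader might infer that a drug acting on heart rate contaminates the signal. The protocol names no agent or vasoconstrictor and mentions no top-ups. Such an effect is possible but is an assumption.
- A reader might infer that a change in top-ups caused by music would bias the result. Top-ups occur after assignment, so their effect is part of the total effect of offering music. They are worth reporting by arm, but the trial's comparison is not invalid without them.

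Also, not being listed as data is not the same as being unrecorded: routine charts may hold some of these details. That softens the point without removing it, because charts are unlikely to place events on the physiological recording.

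**Conclusion.** The concern holds as one of precision and traceability. Extraction type is unrestricted and unstratified, and the protocol does not plan to record it, its duration or the local anaesthetic. The comparison remains valid.

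The size is modest and conditional. With half the cases surgical and a shift of 0.5 to 1 SD, the recoverable variance is about 6% to 20%. The power loss at 20 per arm is about 0.02 (0.87 to 0.85) or 0.08 (0.87 to 0.79) if the planning SD excludes this variation, and nil if it includes it. The mix and the shift are assumptions that the documents cannot confirm. The loss of the means to examine surgery by arm does not depend on them, except so far as routine charts fill the gap.

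**What to change.** - **Before allocation**, classify each case as simple or surgical. Either keep one envelope set per class and analyse within class, or keep a single set and adjust the arm comparison for class.
- **On the existing recording**, mark local anaesthetic injection, start of extraction and end of procedure.
- **On the record form**, log extraction duration and the local anaesthetic agent, any vasoconstrictor, amount and top-ups. Report these by arm.
- **In the analysis**, compare the arms over the same event-anchored windows. Their exact definition can sit in the SAP, provided the marks exist.
- **Adjust only for the pre-allocation class.** Duration and top-ups arise after randomisation and may themselves be affected by music, so describe them and do not adjust for them.

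The choice and amount of local anaesthetic stay with clinical practice. The cost is a few form fields and event marks and, if stratified, a second envelope set with smaller strata.

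### No stated analysis uses the baseline measures the protocol collects; prespecify ANCOVA on pre-procedure STAI, and on HRV and haemodynamics only if their baseline precedes the music

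*Protocol*

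**What the plan says.** Protocol section 4.1 gives one analysis statement: "the two groups, the control group and the music group, will be statistically compared and analyzed using the analysis software GraphPad Prism6". Its Analysis Method entry adds only that a statistical comparison will be made in that package. No test, outcome scale (post value, change or repeated measures) or covariate is named, and none is ruled out.

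Section 4.1 also provides for data that could serve as baselines:
- "The Modified Dental Anxiety Scale (MDAS) will be administered before the start of the treatment".
- STAI is given twice, once ahead of extraction and once on completion.
- "Recording of heart rate variability and circulatory dynamic will begin 15 minutes before the start of the procedure while wearing headphones".

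No pre-procedure EEG is mentioned, although section 2 lists EEG among the primary items. Section 4.2 says that autonomic, EEG and haemodynamic parameters are collected during treatment and mentions no earlier period.

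On design, "Forty patients will be randomly assigned to two groups of 20 patients each" by the envelope method, with no stratification mentioned. Section 4.4 states that "α value 0.05, β value 0.2, effect size 1SD were used as the basis for setting the number of cases". It names no outcome for that effect and uses no baseline correlation.

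**The concern.** With 20 patients per arm and no stratification mentioned, some baseline difference in anxiety or autonomic tone will often arise by chance. Where a baseline predicts its outcome, adjusting for it removes that part of the outcome variance and corrects for the imbalance that occurred. The measurements are already planned, but nothing in the protocol says they will be used this way. If the two-group comparison is made without them, the estimate is less precise than the same 40 patients could give. This matters most if the true effect is below the 1 SD assumed in section 4.4, which is a large effect.

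**Working it through.** **Inputs from the protocol.** Total 40, so 20 per arm (sections 4.1 and 4.4); α 0.05, β 0.2, effect 1 SD (section 4.4).

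**Assumptions.** Two-sided test, because sidedness is not stated. Baseline–outcome correlation ρ is not in the documents and is shown at 0, 0.3, 0.5 and 0.7. The 0.8 SD effect is an illustration, not a protocol figure.

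**Step 1: the protocol's 40.** A two-sample t-test (noncentral t) at 1 SD needs 17 per arm, total 34, for 80% power. A total of 40 results from a Wilcoxon–Mann–Whitney test with the minimum relative efficiency of 0.864 (20 per arm), or from 34/0.85 = 40 with an assumed 15% dropout. The protocol does not say which was used. Neither uses baseline information.

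**Step 2: unadjusted power at 20 per arm.** The noncentrality is d·√(20/2) with 38 df.
- d = 1: 1 × 3.162 = 3.162, power 86.9%.
- d = 0.8: 0.8 × 3.162 = 2.530, power 69.3%.
- Effect detectable with 80% power: 0.909 SD.

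**Step 3: ANCOVA with one baseline.** The residual SD is multiplied by √(1−ρ²). Estimating the slope inflates the variance by 1 + 1/36. The noncentrality becomes d·√10 / √[(1−ρ²)(1+1/36)] with 37 df. For example, at ρ = 0.5 and d = 0.8 the divisor is √(0.75 × 1.0278) = 0.878, so the noncentrality is 2.530/0.878 = 2.88 and the power is 80.1%.

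| Analysis | 1−ρ² | Power at 0.8 SD | Power at 1 SD | Detectable at 80% power |
|---|---|---|---|---|
| Unadjusted | – | 69.3% | 86.9% | 0.909 SD |
| ANCOVA, ρ = 0 | 1.00 | 68.1% | 85.9% | 0.922 SD |
| ANCOVA, ρ = 0.3 | 0.91 | 72.2% | 89.0% | 0.880 SD |
| ANCOVA, ρ = 0.5 | 0.75 | 80.1% | 93.9% | 0.799 SD |
| ANCOVA, ρ = 0.7 | 0.51 | 92.5% | 98.9% | 0.659 SD |

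Simulation at 1 SD gave 86.5%, 93.6% and 98.9% for ρ = 0, 0.5 and 0.7, in line with the table. Break-even is at about ρ = 0.2.

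**Step 4: chance imbalance.** The standard error of a baseline difference is √(2/20) = 0.316 SD. The chance of an absolute difference above 0.3 SD is 34%, and above 0.5 SD it is 11%. By normal approximation, the unadjusted type I error conditional on the imbalance is:

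| Baseline difference | ρ = 0.5 | ρ = 0.7 |
|---|---|---|
| 0 | 2.4% | 0.6% |
| 0.3 SD | 4.6% | 3.5% |
| 0.5 SD | 8.9% | 11.6% |

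Averaged over randomisation, the error is 5%.

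**Step 5: which baselines are usable.**
- STAI: measured before and after, so its own pre-procedure score can be the covariate, provided it is completed before any music.
- MDAS: measured once, so it can serve only as an extra prognostic covariate.
- HRV and haemodynamics: section 4.1 starts recording 15 minutes before the procedure with headphones on and places the music during extraction. Section 4.2 places collection during treatment. Section 5.2 speaks of listening before sedation takes hold. If music plays in the early window, that window is not a pre-intervention baseline, and adjusting for it could remove part of the effect.
- EEG: no pre-procedure recording is stated.

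**The case against.** The strongest reply is that the protocol makes no wrong choice here. It names no test. ANCOVA, change scores and repeated-measures models are all comparisons of two groups, and the details are commonly left to an SAP, which is not at hand. Much of this stands. A reader might infer that the protocol commits to a plain unadjusted test and throws the baselines away; the text does not say so. What remains is that the protocol has an analysis-method entry, commits there to one contrast in one package, and gives the baselines no role.

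Three other stronger readings also go too far:
- **That the unadjusted comparison is invalid.** It keeps 5% type I error overall. The conditional error exceeds 5% at a 0.5 SD imbalance, which has only an 11% chance of being exceeded, and is below 5% at 0.3 SD or less.
- **That the trial is short of power.** At its own 1 SD it has 86.9%, above the planned 80%.
- **That adjustment is free.** It costs one degree of freedom, gains nothing below about ρ = 0.2, and rests on a correlation the documents do not give.

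The reply is also right that a blanket instruction to adjust every primary variable for its own baseline would fail: EEG has none, and the HRV and haemodynamic window may not precede the music.

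**Conclusion.** The point holds as a recommendation to prespecify a better method, not as an error that invalidates the trial. The collected baselines have no stated analytic use, and adjusting for one of them is very cheap. At 0.8 SD the gain is about 3, 11 or 23 percentage points of power for ρ of 0.3, 0.5 or 0.7; at 1 SD it is about 2, 7 or 12 points. If ρ is near zero, about one point is lost. These figures assume a two-sided 5% test, normally distributed outcomes, 20 analysed per arm and a covariate measured before the intervention. That last condition can be met for STAI. For HRV and haemodynamics it is unresolved, and EEG has no stated baseline.

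**What to change.** In section 4.1, Analysis Method, state that post-procedure STAI is compared between groups by ANCOVA, with group as factor and pre-procedure STAI as covariate. MDAS may be added as a second covariate, at the cost of one more degree of freedom. Allow any package that fits the model.

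Reconcile sections 4.1, 4.2 and 5.2 on when recording starts and when music starts. If a segment is confirmed to precede any music, apply the same model to the HRV and haemodynamic outcomes with that segment as covariate, using log-transformed HRV power. If no such segment exists, do not adjust for that window. Leave EEG out of the baseline-adjusted model as long as no pre-procedure EEG is specified.

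The cost is wording and one degree of freedom per model. No extra patients or measurements are needed.
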